### Evaluation Outcomes

The *Health in work* program and the Inclusive Work Agreement have several complex, nongraded aims, which focus on improved work environment, sustainable job participation, and prevention and reduction of sickness absence. The *Health in work* program especially pinpoints work participation as an aspect that contributes to better health. However, it is not known to what extent the systematic intersectoral collaboration between NAV and specialist health services in HIW interventions is an effective use of resources. Therefore, it is impossible to define a single primary OM for this trial and, thus, the four primary OMs are as follows: (1) change in overall sickness absence rates (self- and physician-certified) at the workplace (unit level) in percentage of planned workdays for the period 24 months before allocation compared with the period 12-24 months after allocation (OM 1); (2) change in health care use, assessed using data from the National Register of Control and Health Service Refunds (The Norwegian Directorate of Health) and the Norwegian Patient Register (The Norwegian Directorate of Health), for the period 24 months before allocation compared with the period 12-24 months after allocation (OM 2); (3) change in health-related quality of life, measured using the EQ-5D-5L and EQ VAS for the period from enrollment to 24 months after allocation (OM 3); for OMs 1-3, changes within and between trial arms will be analyzed); and (4) health economic analyses comprising cost-effectiveness analyses based on OM 3 and cost-benefit analyses based on OMs 1 and 2 comparing the trial arms in terms of incremental costs based on direct and indirect costs related to the interventions throughout the intervention period (OM 4).

Secondary OMs focus on health complaints, anxiety, and different aspects of work and work environment and comprise the following: change in physician-certified mean sickness absence rates (individual level) based on data from the Norwegian National Register of Sickness Absence (NAV sykefraværsregister) for the period 24 months before allocation compared with the period 12-24 months after allocation (OM 5); change in self-certified sickness absence rates (individual level; OM 6); change in psychosocial work environment, assessed using the Demand–Control–Support Questionnaire score (OM 7); change in social support from colleagues, assessed using the Nondirective and Directive Support Survey score (OM 8); change in job satisfaction, assessed using the Global Job Satisfaction score (OM 9); change in subjective health complaints, assessed using the subjective health complaints score (OM 10); change in health anxiety, assessed using the Whiteley index score (OM 11); and change in satisfaction with life, assessed using the Satisfaction With Life Scale score (OM 12).

OMs 6-12 are based on data from the trial questionnaires. Changes within and between trial arms will be analyzed for the following periods: enrollment to 12 months after allocation and enrollment to 24 months after allocation for each OM and 12 to 24 months when relevant.

For in-depth details regarding OMs, see ClinicalTrials.gov.

The trial questionnaire collects information on background variables (ie, type of employment, height, weight, education, income, smoking habits, alcohol consumption, and physical activity) as well as self-reported sickness absence and health care use. Several sections of the trial questionnaire are the same as those in the seventh and latest survey of the Tromsø Study (Tromsø 7), which took place in 2015-2016. For trial participants who also participated in Tromsø 7 and provided explicit consent, trial data will be linked to Tromsø 7 data to obtain an impression of natural intraindividual variation over time.

For all analyses, the possible impact of the COVID-19 pandemic will be addressed.

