### Data Collection and Management

Trial questionnaires are electronic and administered by REDCap (Research Electronic Data Capture; Vanderbilt University) tools. Completed questionnaires are double-checked manually with informed consent forms to guarantee that only the data of those who have provided consent are used. Informed consent forms contain three sections to obtain separate consent for each of the following: use of questionnaire data, linkage to register data, and linkage to data from Tromsø 7, if applicable (Multimedia Appendix 1).

When answering questionnaire 1 at enrollment, participants registered their email address, to which links for later questionnaires will be mailed. Questionnaires 2 and 3 are completed at 12 and 24 months after allocation, respectively, or as appropriate owing to pandemic-related delays.

Questionnaires 1-3 all have the same questions on health-related quality of life, symptoms, work environment, and individual self-certified sickness absence. Validated questions were used when possible (see *Evaluation Outcomes* and Figure 2). Individual physician-certified sickness absence and health care use data are collected through register data for the period from 24 months before allocation to 24 months after allocation.

During the intervention period, workplaces report the time used for intervention activities on a quarterly basis. The sickness absence rate at the unit level is reported for the periods 24 months before allocation to allocation, the intervention period, and 12-24 months after allocation. Intervention staff registers the time spent on the preparation and execution of the intervention.

Workplaces that withdraw from the interventions before completing the intervention period are asked to continue to report their sickness absence data, and the individual participants are encouraged to answer all questionnaires, enabling intention-to-treat (ITT) analysis.

Data are stored on a secure research server at UNN with restricted access, which will also be used for data analysis. The personal national identification number will be used to collect register data according to consent. Data access is restricted to the project research group.

Study-specific personal identifiers will be used for all data storage, linkage, and analysis. The key list of identifiers is kept separate from the remaining data; access is restricted to PI NF and co-PI [name].

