#### Analysis of Data

Difference-in-difference analyses will be used to address any differences in sickness absence, health care refunds, and health-related quality of life between the trial arms at the unit level. Cost-effectiveness and cost-benefit analyses will compare the trial arms in terms of incremental costs based on direct and indirect costs related to interventions throughout the intervention period.

At the individual level, outcomes will be analyzed based on changes from enrollment. Moreover, 2-tailed *t* tests or Mann-Whitney *U* tests and chi-square tests will be used when appropriate. A generalized linear mixed effects Poisson model will be used to investigate possible differences in percentage of sick leave between the 2 trial arms. A multivariable, multilevel logistic, ordered logistic, and linear regression allowing for clustering at the unit level will be used according to the outcome measure (OM) analyzed. To consider changes owing to the pandemic-related temporary halt of the study, other statistical methods such as stratification will be relevant.

We will use 2-sided *P* values with *α*<.05 level of significance for all tests.

The analysis will be according to ITT regardless of protocol adherence.

Results will be reported in line with CONSORT (Consolidated Standards of Reporting Trials) guidelines.

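### Primary outcome OM 2 sets 24 months of health care use against a 12-month window without a rate denominator, so the planned change is not on a common time scale

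*Protocol article*

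**What the plan says.** All references are to the Protocol article.

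- **Outcome.** Evaluation Outcomes lists OM 2 among four primary outcomes: "change in health care use, assessed using data from the National Register of Control and Health Service Refunds" and the Norwegian Patient Register, "for the period 24 months before allocation compared with the period 12-24 months after allocation (OM 2".
- **Data span.** Data Collection and Management confirms the length of the pre-period: "health care use data are collected through register data for the period from 24 months before allocation to 24 months after allocation".
- **Neighbouring outcomes.** OM 1 has the same windows but is expressed "in percentage of planned workdays for the period 24 months before allocation compared with the period 12-24 months after allocation (OM 1". OM 5, also with the same windows, is "change in physician-certified mean sickness absence rates (individual level".
- **Analysis.** Evaluation Outcomes adds "for OMs 1-3, changes within and between trial arms will be analyzed". Analysis of Data says "Difference-in-difference analyses will be used to address any differences in sickness absence, health care refunds, and health-related quality of life between the trial arms", at unit level. It names no offset, annualisation or person-time for refunds. The Poisson mixed model in that section is for percentage of sick leave.
- **Onward use.** OM 4 includes a cost-benefit analysis built on OMs 1 and 2, comparing the arms on incremental costs.
- **Further detail.** Evaluation Outcomes refers the reader to the trial registry for details of the outcomes. That record was not available for this review.

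**The concern.** A percentage of planned workdays, or a mean absence rate, does not depend on how long the window is. An amount of health care does: two years of contacts or refunds are about twice one year of them. OM 2 uses the window phrase of OM 1 for an amount and supplies no denominator.

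Two planned analyses are affected if totals are used. The within-arm change would contain a fall produced only by the window lengths. The unit-level difference-in-difference would give the pre-period twice the weight it should have, so that precision is lost and a chance difference between the arms before allocation pulls the estimate. OM 2 is a primary outcome, and its within-arm change is an announced result.

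**Working it through.** The document gives no mean, SD or sample size for OM 2, so there is no planned figure to reproduce. The check is window arithmetic followed by variance algebra under stated assumptions.

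**Inputs from the document.** Pre-window 24 months; post-window months 12 to 24, which is 12 months; 45 workplaces allocated to Health in work (HIW) and 52 to inclusive work measures (IWM) (Results).

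**Within arm.** With constant use, post/pre = 12/24 = 0.50, a change of -50% with no effect. With a true 10% reduction, 0.9 × 12/24 = 0.45, a change of -55%.

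**Between arms, additive scale.** Let *y* be post-window use (one year) and *x* the annualised pre-window use. The change in totals is *y* - 2*x*; the annualised change is *y* - *x*. The arm difference in *x* therefore enters with weight 2 instead of 1.

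Assumed model: annual use of a unit = mean + stable unit part + independent yearly noise, with total variance 1 and stable share ρ. Then:

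- change in totals: ρ + 3(1 - ρ)
- annualised change: 1.5(1 - ρ)
- post-window rate adjusted for the pre-window rate: 1 - ρ²/(ρ + (1 - ρ)/2) = 1 - 2ρ²/(1 + ρ)

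| ρ (assumed) | Totals | Annualised | Baseline-adjusted | Variance ratio, totals/annualised | SE ratio |
|---|---|---|---|---|---|
| 0 | 3.0 | 1.50 | 1.00 | 2.00 | 1.41 |
| 0.3 | 2.4 | 1.05 | 0.86 | 2.29 | 1.51 |
| 0.5 | 2.0 | 0.75 | 0.67 | 2.67 | 1.63 |
| 0.7 | 1.6 | 0.45 | 0.42 | 3.56 | 1.89 |
| 0.8 | 1.4 | 0.30 | 0.29 | 4.67 | 2.16 |

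A comparison that ignored the pre-period altogether has variance 1. Over this range the SE for totals is √1.4 = 1.18 to √3.0 = 1.73 times as large, so subtracting the unscaled baseline is worse than not using it.

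**Simulation.** 5,000 Poisson-gamma trials with 45 and 52 workplaces; assumed 5 contacts per person-year, 10 persons per workplace and workplace frailty variance 0.3 or 0.1.

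- Within-arm change with no effect (frailty variance 0.3): -49.98% on totals; mean change -5.00 contacts on totals and 0.00 annualised.
- Mean additive difference-in-difference on totals (frailty variance 0.3): 0.009 with no effect, and -0.503 when the true effect is -0.5. There is no systematic bias.
- Movement of the estimate per unit of annual baseline imbalance: about -1.04 to -1.09 on totals, against about -0.04 to -0.09 annualised.
- SD of the difference-in-difference with no effect: 0.617 on totals against 0.174 annualised (frailty variance 0.3), and 0.411 against 0.178 (frailty variance 0.1). These settings imply ρ = 7.5/8 = 0.94 and 2.5/3 = 0.83, above the range in the table, so the penalty is larger still.
- Log-ratio scale, no effect (frailty variance 0.3): mean between-arm difference 0.000. The factor of two cancels.

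**The case against.** The strongest reply is that the document never says totals will be subtracted. One period is to be compared with another, and that wording fits use per year just as well. The authors handle the same windows as rates in OM 1 and OM 5, they refer to the registry for outcome detail, and an analysis plan may annualise. This stands as a limit: every consequence above is conditional on totals. It does not remove the point. The windows are fixed here for a primary outcome, they are unequal, and the denominator written for OM 1 and OM 5 is missing for OM 2.

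A reader might also infer more than the document supports:

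- **That the between-arm result is biased.** It is not. Under randomisation the halving is common to both arms and cancels on average on the additive scale, and it cancels outright on a ratio scale.
- **That OM 4 would show false savings.** OM 4 compares the arms on incremental costs, so a halving common to both arms cancels in expectation.
- **That the variance penalty is fourfold.** With equal SDs for the 24-month and 12-month rates and a correlation of 0.5, the variances are 5 - 4(0.5) = 3.0 for totals and 1 - 0.5² = 0.75 for baseline adjustment. That ratio mixes the window effect with the separate gain from covariate adjustment, and it ignores that averaging over two years normally lowers the SD. The window effect alone, with that averaging allowed for, is 2.67 at ρ = 0.5.

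It may also be said that replacing the difference-in-difference is a preference. Scaling alone does remove the defect; the further gain from baseline adjustment is smaller (0.75 to 0.67 at ρ = 0.5), but it needs no data beyond those already collected.

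**Conclusion.** The point holds in conditional form. As written, OM 2 lacks the time scale that its unequal windows require. If totals are compared, the within-arm change is -50% when nothing has changed; this follows from the windows alone. The additive between-arm estimate remains unbiased but counts baseline imbalance twice, with 2.0 to 4.7 times the variance of the annualised version for ρ from 0 to 0.8. That size rests on the assumed variance model, because the document gives no variability for OM 2. On a ratio scale the between-arm problem disappears, while the within-arm halving remains. The definition should be corrected before OM 2 is analysed.

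**What to change.** 1. In the OM 2 definition, state use as contacts and refunds per person-year in each window.
2. For the arm comparison, replace the unscaled difference-in-difference with a model for the month 12-24 rate that has the 24-month pre-allocation rate as covariate and allows for clustering by workplace. At ρ = 0.5 the variance goes from about 2.0 (totals) to 0.75 (annualised change) or 0.67 (baseline-adjusted).
3. Report any within-arm change on the per-person-year scale only.
4. Use the same scale where OM 2 enters OM 4.

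The cost is a sentence in the outcome definition and a matching one in the analysis plan. The register data already cover both windows, so nothing new has to be collected. If the registry record or an analysis plan already annualises OM 2, step 1 only brings this text into line with it.

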### Interventions

#### HIW Intervention

Personnel from the NWCs and specialist health services work in collaboration to provide HIW interventions according to a standardized protocol. An initial meeting is held to define the workplace’s goals and plan the course of the intervention, followed by three 1.5-hour sessions over a 12-month period. During these sessions, health personnel present structured health information about musculoskeletal, pain, and mental disorders, and NAV personnel put this information in the context of work and the specific workplace. Between sessions, group-based workplace process exercises are carried out. During these exercises, challenges related to session content as well as topics around the work environment and work inclusion should be addressed.

In more detail, the first session aims to use health information on common neck and back complaints to increase workers’ ability to cope with them as individuals and collectively. It also presents tasks that foster reflection and dialogue on factors that promote the health and inclusion of workers with musculoskeletal complaints in the workplace. The second session aims to communicate health information regarding pain to increase workers’ ability to cope with it individually and collectively. The third session is similar to the first but with content related to common mental health complaints.

Both the sessions and the group exercises between the sessions should involve all workplace staff (management and employees). The group exercises should be active meetings that take place without the involvement of intervention personnel. Finally, at the end of the 3 sessions, an evaluation meeting is held to discuss possible further follow-up.

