### Timeline

Upon agreement to participate in the trial, all employees and management at the workplaces received the following by email from their employer: information about the trial, a PDF file with the individual informed consent form, and a link to questionnaire 1. Completed paper forms with individual informed consent were collected for 2 weeks, and then the random allocation was executed. Intervention periods were scheduled to be 12 months for both trial arms. Questionnaires 2 and 3 were to be completed 12 months and 24 months after allocation, respectively. Owing to the global pandemic, the trial was halted between mid-March 2020 and September 2020, and activities were reduced at several time points. Therefore, the intervention period and time points for questionnaires 2 and 3 were adjusted for workplaces included before April 2020 and in fall 2020, whereas workplaces included in 2021 were expected to follow the usual timeline. A flowchart of the study process is shown in Figure 1, and the timeline is shown in Figure 2.

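### The cost-benefit part of primary outcome OM 4 charges delivery costs over the intervention period but, as written, leaves out differences in absence and health care use during months 0-12

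*Protocol article*

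**What the plan says.** OM 4 is one of four primary outcomes. Its cost-benefit half is described in Evaluation Outcomes as "cost-benefit analyses based on OMs 1 and 2".

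- **Gains.** OM 2 is defined "for the period 24 months before allocation compared with the period 12-24 months after allocation (OM 2"). OM 1, workplace absence, has the same window. Neither covers the first year after allocation.
- **Costs.** Evaluation Outcomes counts "incremental costs based on direct and indirect costs related to the interventions throughout the intervention period (OM 4"). Analysis of Data repeats the limit: "incremental costs based on direct and indirect costs related to interventions throughout the intervention period".
- **Length of the cost window.** Timeline states: "Intervention periods were scheduled to be 12 months for both trial arms". It adds that, owing to the pandemic, "the intervention period and time points for questionnaires 2 and 3 were adjusted for workplaces included before April 2020 and in fall 2020".
- **Data.** According to Data Collection and Management, unit-level absence is reported for "24 months before allocation to allocation, the intervention period, and 12-24 months after allocation". Register data on physician-certified absence and health care use run from two years before to two years after allocation. Workplaces report time spent on intervention activities quarterly while the intervention runs.

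**The concern.** Under Rationale of the Trial, the economic question is whether the costs of HIW, described there as resource-demanding, outweigh those of sick leave and lost quality of life. An answer needs every consequence of the programme over a stated horizon, set against its cost. On the scheduled timeline the programme's cost falls in months 0-12, and the savings (or losses) credited to it come only from months 12-24. The HIW sessions are spread over the first year, so absence and health care use may already differ between arms in that year, in either direction. Such a difference would not reach the balance, and OM 4 could then misstate whether HIW pays for itself.

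Leaving the first year out can be reasonable for an effect outcome that looks for a lasting change. The problem arises only when the same window is carried over into a cost balance.

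**Working it through.** **Step 1: windows side by side (scheduled timeline, months from allocation)**

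| Component of OM 4 | Months 0-12 | Months 12-24 | Source |
|---|---|---|---|
| Intervention costs | counted | not counted | Evaluation Outcomes; Analysis of Data; Timeline |
| Absence (OM 1), cost-benefit | not counted | counted | Evaluation Outcomes |
| Health care use (OM 2), cost-benefit | not counted | counted | Evaluation Outcomes |
| Quality of life (OM 3), cost-effectiveness | inside the span | inside the span | Evaluation Outcomes |

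The gap is in the two cost-benefit gain rows. For workplaces with an adjusted intervention period the cost window may not be months 0-12, but the OM 1 and OM 2 windows are still defined from allocation and still omit months 0-12.

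**Step 2: size.** The article states no net benefit, cost or first-year effect, so there is no figure to reproduce. Simple accounting shows the range. Let

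- B2 = gain in months 12-24, taken as positive;
- r = gain in months 0-12 divided by B2 (assumption);
- c = incremental intervention cost divided by B2 (assumption).

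Net benefit as written = B2 × (1 - c). Net benefit over months 0-24 = B2 × (1 + r - c). The difference is r × B2, whatever the cost. The ratio is (1 + r - c)/(1 - c):

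| c | r = -0.25 | r = 0 | r = 0.5 | r = 1 |
|---|---|---|---|---|
| 0 | 0.75 | 1.00 | 1.50 | 2.00 |
| 0.25 | 0.67 | 1.00 | 1.67 | 2.33 |
| 0.5 | 0.50 | 1.00 | 2.00 | 3.00 |
| 0.9 | -1.50 | 1.00 | 6.00 | 11.00 |
| 1.2 | 2.25 | 1.00 | -1.50 | -4.00 |

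A negative entry is a change of sign. At c = 1.2 and r = 0.5, a loss of 0.2 × B2 becomes a gain of 0.3 × B2. At c = 0.9 and r = -0.25, a gain of 0.1 × B2 becomes a loss of 0.15 × B2.

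**Step 3: illustration in working days per employee.** Power Calculation gives a target fall from 6.6% to 5.9%, or 0.7 percentage points. With 230 planned workdays a year (assumed), B2 = 0.007 × 230 = 1.61 days. HIW session time is 3 × 1.5 = 4.5 hours; with a 7.5-hour day (assumed) this is 0.6 day. Take that as the only incremental cost (assumed), so c = 0.6/1.61 = 0.37.

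- As written: 1.61 - 0.6 = 1.01 days.
- Months 0-24, r = 0.5: 1.5 × 1.61 - 0.6 = about 1.8 days, a factor of 1.80.
- Months 0-24, r = 1: 2 × 1.61 - 0.6 = 2.62 days, a factor of 2.59.

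If the cost is 9 hours instead (1.2 days), the net as written is 0.41 day and the factors are 2.96 and 4.93. With r = 0 the factor is 1 in every case.

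**The case against.** **The article is condensed, and costing rules belong in a full analysis plan.** Basing the analysis on OMs 1 and 2 might name only the measures and not their windows. This would settle the matter if the article were silent. It is not: it defines both outcomes by their windows and gives the cost window in two sections.

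**Indirect costs during the intervention period could include productivity lost to absence.** Unit-level absence is collected for that period, and on this reading year-1 absence would be counted. But both sections tie the costs to the interventions, and neither says that absence is among them. If it is intended, the article should say so.

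**Delivery costs are properly charged when they arise.** This stands. Setting an up-front cost against a later gain is ordinary investment accounting. The cost window is not itself the fault; the omitted first-year consequences are.

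**The pandemic adjustment means the windows need not be disjoint everywhere.** This also stands, and the mismatch should be described as that of the scheduled timeline. It does not bring months 0-12 back into OMs 1 and 2.

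A reader might infer two further faults that the article does not support. One is that the cost-effectiveness ratio shares the defect. OM 3 spans both years, and the 12-month questionnaire repeats the quality-of-life questions, so first-year quality of life is not cut off. The other is that second-year delivery costs are known to be missing. For HIW the article says only that "an evaluation meeting is held to discuss possible further follow-up", and for IWM that meeting is optional. Follow-up delivery is a possibility, and its amount is not given.

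**Conclusion.** The point holds for the cost-benefit part of OM 4 only. As written, first-year differences in absence and health care use enter neither of the outcomes that supply the gains, while the delivery costs of the intervention period are charged. If HIW helps in year 1, net benefit is understated by the year-1 gain. If absence or health care use rises in year 1, net benefit is overstated by that loss.

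The size cannot be stated from the article. It is nil if there is no first-year effect, a factor of 2 to 3 if cost is half the year-2 gain and the year-1 gain is 50-100% of it, and possibly a change of sign when cost exceeds the year-2 gain. All of these rest on assumed values of r and c.

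A reader might infer that net benefit is wrong by a factor of 1.5 to 2. That range is 1 + r for r between 0.5 and 1. It describes gross benefit, equals the net-benefit factor only at zero cost, and has no support in the article.

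**What to change.** In Evaluation Outcomes (OM 4) and Analysis of Data, state that the cost-benefit analysis uses one horizon, from allocation to month 24:

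- Compute the between-arm differences in absence and health care use over months 0-24, adjusted for the pre-allocation rate.
- Charge intervention delivery costs in either arm whenever they occur within the horizon, including any agreed follow-up activity.
- Leave OMs 1 and 2 as they are for the effect analysis.
- For workplaces with an adjusted intervention period, divide reported absence at month 12 so that no days are counted twice or lost.

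**Cost.** The outcome side needs wording only: register data already run to month 24, and workplaces already report absence for the intervention period and for months 12-24. The small downside is on the cost side. Workplaces' time reports are tied to the intervention period, so any follow-up activity after it needs continued reporting or an estimate.
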